## Outcome measures

### Anthropometry

Weight will be measured to the nearest 0.1 kg using a Seca digital portable scale (model 813 Seca gmbh & Co., Hamburg, Germany) with the participant wearing minimal clothing. Participants will be briefed about the importance of taking accurate weight measurements. HIV-infected people lose a considerable amount of weight before they seek medical care and clothes become very loose. To keep clothes in shape, many women wear several layers of clothing and if left unchecked, these could add considerably to the body weight. Each participant will be given a pre-weighed piece of cloth (two yard) to tie around their body at the time of measurement. All other clothes and accessories, with exception of underwear, will be removed.

Height will be measured to the nearest 0.1 cm using a free-standing Seca stadiometer (model 225 Seca gmbh & Co., Hamburg, Germany). A standard procedure for measuring height, without shoes and socks, will be followed. Height, if accurately measured, should remain constant across the duration of the study. However, it is common for African women to have elaborate hair styles that cannot be undone for the purpose of taking height measurements, therefore, where necessary, extra care will be taken in the estimation of height to account for such hair styles.

Circumference and skinfold thickness measurements will be done simultaneously since similar procedures are used to locate the sites. Three circumference measurements: mid-upper arm, abdominal at the level of the umbilicus, and hip will be taken using a Seca plastic measuring tape. Skinfold thickness will be measured at five sites: bicep, triceps, subscapular, iliac crest and medial calf using a Harpenden skinfold caliper (British Indicators Ltd., London, UK) with all measurements taken on the right side of the body. Standard procedures for the location of sites and taking measurements will be followed [13]. All measurements will be taken in triplicate. Circumference and skinfold thickness measures provide an indication of regional fat distribution. FM as a percentage of total body weight will be calculated from the sum of skinfold thickness measurements (biceps, triceps, subscapular and suprailiac sites = ∑4SF) and prediction equations [14].

### Bioelectrical impedance analysis

Impedance will be measured using a multi-frequency BIA (SFB7 model, ImpediMed Limited, Queensland, Australia) device according to the manufacturer's instructions. This will include ensuring that the battery is fully charged and the equipment is calibrated; participants will be asked not to exercise or take alcohol during the 24 hours before measurement. Participants will rest in a supine position for 5-10 min on a medical examination couch prior to measurement. A very mild current (50 ohms), imperceptible to the participant, passes through the body's water compartments. The SFB7 device takes measurements at 256 discrete frequencies, logarithmically spaced from 4 kHz to 1000 kHz. The software in the device enables the prediction of TBW and by extrapolation, FFM and FM. These prediction equations are population-specific hence there is a need to validate the results using the isotopic technique before the BIA device can be used routinely on HIV-infected people. Prior to analysis, each participant's height, weight, age and sex will be entered into the device.

### Total Body Water

A procedural requirement is that the deuterium oxide dose be administered to a fasted individual or at least two hours after taking a meal. Prior to administering the dose, a baseline saliva sample will be collected from each participant and used to determine the natural baseline enrichment of the isotope in the body. Participants will also be asked whether they have fasted and if not, the time they had their last meal will be noted. Participants will report to the clinic at 08.00 h and the deuterium dose will be administrated between 10.30 h and 11.00 h (as an additional precaution against participants having eaten recently). A pre-weighed dose of 30 g deuterium oxide will be administered orally to each participant regardless of body weight with the aid of a straw, followed by a rinse of the bottle (approximately 50 mL of mineral water) to ensure consumption of the full dose. Participants will be told not to eat, drink or void their bladder within one hour of ingesting the dose and 30 min before collecting the saliva sample. During the equilibration period, the consumption of drinks and emptying the bladder will be restricted. If this is necessary, volumes will be noted. However, due to the extended period of fasting, and period of assessment, participants will be provided with a standard lunch and drink and the volume of the drink will be noted. The first post-dose saliva sample will be collected at four hours after taking the dose and the second post-dose sample at five hours to ensure equilibration.

Saliva samples (4.5 mL) will be collected using a cotton wool ball and with the aid of a syringe and transferred into pre-labelled 5 mL vials and subsequently, pre-labelled zip-lock bags. Saliva samples will be transported in an insulated box cooled with freeze packs to the laboratory at NISIR and stored at -20°C for later analysis.

### Determination of TBW

Deuterium oxide enrichment of the saliva samples will be measured using a Fourier Transform Infrared (FTIR 8400S; Shimadzu, Vienna, Austria) spectrometer. This FTIR is available at the NISIR laboratories in Lusaka, Zambia. Prior to enrichment measurement of the saliva the FTIR will be calibrated using a 99.9 atom % deuterium oxide standard solution of known composition. The standard will be prepared according to the method described in the IAEA guidelines [15] by weighing deuterium oxide and diluting with local drinking water (bottled mineral water) to give a solution of about 1000 mg/kg by weight enrichment. This enrichment of the FTIR calibration standard will be verified using an Isotope Ratio Mass Spectrometer (IRMS) at a reference laboratory (Iso-Analytical Laboratory, UK). A range of enrichments will likely be encountered during analysis of saliva collected from the participants; the accuracy of deuterium oxide analysis over the range will therefore need to be checked by preparing a calibration curve. The 1000 mg/kg enrichment represents the maximum expected body water enrichment. The calibration procedure will involve preparation of deuterium oxide by gravimetric dilution (between 0 and 2000 mg/kg) and measuring their enrichment by the FTIR. Accuracy will be determined from the gradient and linear regression through the data of the calibration curve should be close to 1.

The FTIR will be set up according to IAEA guidelines [15-17]. Once ready to take measurements, the analytical precision of the FTIR will be checked before and after completing the measurements for the day by first taking measurements of local drinking water and the calibrator standard enrichment solution 3 times each and ensuring that the coefficient variation (CV) of less than 1% is achieved. Once the precision is ascertained the enrichment of the saliva samples for the participants will be measured. The spectrum of local drinking water will be obtained first as a background followed by measuring the spectrum of the standard in the range 2300-2800 cm^-1^. Thereafter the spectrum of the saliva will be taken by first obtaining the spectrum of the pre-dose saliva as background then followed by that of the post-dose samples (collected at 4 and 5 h). Prior to obtaining the spectra of the saliva, the samples will be thawed to room temperature and then centrifuged (Model 5702R, Eppendorf AG, Hamburg, Germany) at 3000 rpm for 10 minutes. Once the spectrum has been obtained it will be exported as a text file and further processed using the "isotope.exe" programme developed by the Medical Research Centre (MRC) [17]. This program enables the translation of the spectrum intensity into excess concentration of deuterium oxide in the saliva sample. The dilution space will be calculated from the concentration of deuterium oxide in the saliva using a standard formula. TBW (kg) will be calculated from the dilution space after correcting for non aqueous dilution of deuterium oxide. The dilution space is 1.04 times TBW. The FFM will be derived from TBW using a hydration coefficient, that is the fraction of FFM comprised of water and this is constant in adult, 0.732. Once FFM has been estimated, FM and percentage body fat will be calculated.

Quality control will be done in accordance with the IAEA guidelines [15]. The equation proposed by the IAEA for use as a quality control measure in TBW (kg) = 7.4 × height^3 ^(m^3^), where TBW from each post-dose sample is used with the height of each participant. Since this equation will not be derived from our population in particular, a range incorporating the 95% confidence interval for the above relationship (< 5.7 × height^3 ^or > 9.6 × height^3^) also proposed by the IAEA for assessment of accuracy, will be considered. The TBW samples falling outside this range will be excluded from the analysis. The variation in TBW values depends on both the degree of analytical precision and natural biological variation.

### Clinical assessment

Physical examinations will be undertaken by a medical practitioner and fasting blood sample collected. At baseline and at 12-month assessments, three vials of blood will be collected, for CD4 count, viral load and micronutrient analysis. At 4-month and 8-month follow-ups, all measures except micronutrient analysis will be undertaken. Part of the blood sample for CD4 count will be used to measure full blood count which will be determined at the clinic laboratory. Blood samples will be processed at the clinic laboratory to separate the plasma from the blood cell for CD4 and viral load and the serum for micronutrient analysis. The plasma for viral load and serum for micronutrient determination will immediately be stored at -20°C at the clinic until shipment, while the plasma for CD4 count will be stored at room temperature, packaged and couriered by FedEx to the TDRC in Ndola.

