**Methods/Design:**

This community-based controlled and longitudinal study aims to recruit 200 HIV-infected females commencing ARV treatment at two clinics in Lusaka, Zambia. Data will be collected at four time points: baseline, 4-month, 8-month and 12-month follow-up visits. Outcome measures to be assessed include body height and weight, body mass index (BMI), body composition, CD4, viral load and micronutrient status.

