### Recruitment

Participants will be recruited to the study from women who report to each clinic for care and support after being diagnosed as HIV-positive at a Voluntary and Counselling Treatment (VCT) centre in Lusaka. The clinics will collect blood samples for CD4 count, viral load and liver function tests from each study participant and subsequent appointment times to collect their results will be given. Blood samples collected in all government clinics in Lusaka are analyzed at the Centre for Infectious Diseases Research Laboratories in Lusaka. Upon receipt of results the sister-in-charge at each clinic will screen the results and identify those individuals considered to be eligible to commence ARV treatment based mainly on a CD4 count of 350 cells/μL or less.

Using a tracking system which consists of the participant's residential address and telephone number (or that of their spouse or guardian), eligible participants will be reminded of their clinic appointments. For those who do not have telephone contacts, a clinic staff member will visit them at their respective homes to inform them of their appointment and the need to report to the clinic and the Sister-in-Charge for ART. The sister will then invite each client one by one and explain the nature of the study. Once the client agrees to participate they will be asked to sign a consent form in duplicate or if they are unable to write, they will provide a thumb print. The Sister-in-Charge will sign as a witness. The original copy will be filed at the clinic while the duplicate copy will be stored by the Principal Investigator (PI) in a locked filing cabinet at the project office.

Once the client has consented to the study a project ID number will be assigned and the PI will meet with each individual to work through the information sheet in detail. During this period, each client is provided with another opportunity to clarify any issues or concerns before embarking on the study. Trained nursing and project staff will take routine measurements such as blood pressure and body temperature and also collect a urine sample for a pregnancy test. This will be followed by a full physical examination by a medical practitioner. Once the client has been certified as eligible to commence ARV treatment and meets all inclusion criteria she will be enrolled as a study participant.

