Participants will be eligible if they are HIV-positive with CD4 count 350 cells/μL or less; are commencing ARV treatment; female aged 20-40 years; not mentally challenged and agree to participate in the study. Participants will be ineligible if clinically unstable or with other medical conditions (e.g., elevated creatinine), which will prevent them from commencing on ARV treatment, if they are pregnant or plan to fall pregnant during the study.

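### As written, the sample handling sends separated plasma for the CD4 count, and a cell count cannot be made on that specimen

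*Protocol article*

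**What the plan says.** The abstract (Methods/Design) lists CD4 among the outcomes: "Outcome measures to be assessed include body height and weight, body mass index (BMI), body composition, CD4, viral load and micronutrient status". The eligibility criteria under Recruitment show the unit of measurement: "HIV-positive with CD4 count 350 cells/μL or less".

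The Clinical assessment section plans three vials at baseline and 12 months, for CD4, viral load and micronutrients. The same measures apart from micronutrients are planned at 4 and 8 months, so CD4 is measured at all four visits. On processing, the section says "Blood samples will be processed at the clinic laboratory to separate the plasma from the blood cell for CD4 and viral load", with serum going to micronutrient analysis. Plasma for viral load and serum for micronutrients are stored at -20°C, "while the plasma for CD4 count will be stored at room temperature, packaged and couriered by FedEx to the TDRC in Ndola". The CD4 vial has one other stated use: "Part of the blood sample for CD4 count will be used to measure full blood count which will be determined at the clinic laboratory".

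The Recruitment section describes blood that the clinics take for CD4, viral load and liver function, and adds: "Blood samples collected in all government clinics in Lusaka are analyzed at the Centre for Infectious Diseases Research Laboratories in Lusaka". It names no specimen type.

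**The concern.** A CD4 result in cells per microlitre is a count of cells in a volume of blood. The written procedure removes the cells and ships what is left. The outcome and the specimen do not fit together.

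At stake is a named outcome at every visit. The text reads as an instruction to clinic staff at two sites. If it were followed, the count could not be recovered from the shipped material, because the cells would already have been taken off. CD4 also appears in the sample size section, where CD4 and viral load together carry the largest stated requirement.

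**Working it through.** The main check is a comparison of texts; the only arithmetic is a count of samples.

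**1. What is measured.** Recruitment gives the CD4 threshold in cells/μL. The specimen must therefore contain the cells.

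**2. What is done to the specimen.** Clinical assessment has the clinic laboratory "separate the plasma from the blood cell for CD4 and viral load". Taken alone, this could mean that the cells go to CD4 and the plasma to viral load.

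**3. What is shipped.** The next sentence settles the reading, because it names plasma as the CD4 specimen and gives its storage temperature and destination. The milder reading in step 2 is no longer open.

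**4. Is a usable CD4 specimen described elsewhere?** No. The article nowhere says that whole blood or the cell fraction goes for CD4. The clinic's other use of the vial is a full blood count, and no CD4 count is described there. Recruitment names a laboratory but no specimen.

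Steps 1 and 3 cannot both stand.

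**5. How many samples.** The inputs are 200 women (abstract), four visits (Study design), and anticipated losses of 20% (Dietary intake study) or 25% (Sample size calculation).

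- Ceiling, with no attrition: 200 × 4 = 800.
- With 20% loss, all of it assumed to occur before month 4: 200 + 3 × 160 = 680.
- With 25% loss on the same assumption: 200 + 3 × 150 = 650.

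The text therefore governs about 650 to 800 CD4 samples. This is the reach of the wording, not an estimate of samples actually lost.

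**6. What else depends on CD4.** The Statistical Analysis plan section names nutritional status and body composition as the primary outcome variables. The Sample size calculation gives 48 per group for weight and 58 for fat-free mass, neither of which uses CD4. The 88 per group is stated for CD4 and viral load together. These figures are taken as stated and were not re-derived here.

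**The case against.** The strongest reply is that one word is wrong and the plan is not. The section provides a separate vial for CD4, draws on it for a full blood count, and keeps it at room temperature while the viral-load plasma and the serum go to -20°C. All of this fits an unseparated CD4 sample. A journal article also condenses a fuller protocol, and laboratory handling usually sits in that document. This reply stands as an account of how the error arose and limits its weight. It does not remove the error: the article goes beyond leaving handling out and states a specimen that is wrong for the test.

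A reader might infer three stronger points, which the document does not support.

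- **Two laboratories are used for outcome CD4.** Recruitment says samples are "analyzed at the Centre for Infectious Diseases Research Laboratories in Lusaka", while Clinical assessment sends CD4 to Ndola. But the Recruitment blood is taken to decide ARV eligibility, before the study is explained and consent is given. Clinical assessment names a single destination for the study's CD4 samples. Two laboratories for two purposes is not a contradiction. Recruitment does refer loosely to study participants when it describes the eligibility blood, so a clarifying sentence would help.
- **CD4 change is distorted by regression to the mean from the 350 cut-off.** This needs the screening result to serve as baseline. Nothing says it will, and a baseline-visit CD4 vial is already planned. Even if it did, the shift would fall on both randomised arms and would not by itself bias the comparison between them.
- **The sample size loses its basis.** The 88 per group is stated for viral load as well as CD4, so it does not rest on CD4 alone.

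**Conclusion.** The point holds for the procedure as written. The Clinical assessment section assigns separated plasma to a cell count, and that specimen cannot yield the CD4 outcome at 0, 4, 8 or 12 months. The wording covers at most 800 samples before attrition. The conclusion rests only on the article's own unit for CD4 and its own description of the specimen.

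It should not be read as showing that the trial failed, or will fail, to measure CD4. That would require staff to follow the phrase literally, and the surrounding details suggest a slip in drafting. The primary outcomes and their analysis are untouched. The correction should be made because the outcome is a named one and the change is almost free.

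**What to change.** In Clinical assessment, correct the specimen description. After the portion for the full blood count is taken, the CD4 vial is kept and shipped as unseparated whole blood at room temperature, and plasma is separated only from the viral-load vial. The laboratory instructions at both clinics should be checked for the same wording. Further handling requirements belong in the laboratory's own procedure, and the article need not give them.

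Optionally, add a sentence saying that the Lusaka result under Recruitment is for ARV eligibility screening, and that the baseline-visit sample under Clinical assessment is the CD4 baseline.

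The cost is a text correction. The vials, the room-temperature storage and the courier are already planned, and neither the sample size nor the analysis changes.

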### Dietary intake study

A 3-day weighed food record coupled with a 24-h dietary recall technique will be used to determine the dietary pattern and the nutrient intake of the participants. Ten individuals with knowledge of nutrition will be recruited from various government institutions as "field staff". Training will include pre-testing on both 3-day weighed food records and 24-h dietary recall methodologies. Twenty participants will be recruited for the pre-test from another clinic in Lusaka offering ART services but not involved in the main study.

It is common practice for HIV-infected people to seek care and support from a health facility far from their residential catchment area. Therefore, it will be expected that many participants may be located in a wide range of residential locations of Lusaka including urban, peri-urban and rural areas. A well-designed house location plan will be required. Final updates on the residential address of each participant will be collected when they come for the 8-month follow-up visit. A participants' register to aid clustering based on their residential location will be prepared to assist in assigning participants within close proximity to the same field staff. In addition to telephone and house numbers, detailed directions to the participant's residence will be taken, including names of nearby landmarks such as schools, churches, and shops. It is also important to note the local names used to identify participants in their local communities. For example, it is common for women in Zambia to be called by their children or husband's names.

Visiting participants in their home might not be acceptable as some participants might not wish to disclose their HIV status to some or all members of their household. Participants will be assured that the all dietary intake data will be collected by non-medical personnel. This component of the study will be led by the National Food and Nutrition Commission which is well known as an institution responsible for promoting the nutrition agenda in the country which should help to minimize any potential stigma.

A total of 200 participants will be recruited for the study and a drop-out rate of 20% is anticipated. Accordingly, we anticipate that dietary intake data will be collected from approximately 160 participants. Each field staff member will be assigned 2 participants per day therefore we anticipate that data collection will take about two months to complete. Each participant will be contacted a week before data collection to remind them of the visit by field staff. Wherever possible, an understanding of level of literacy will be established beforehand. For participants who are unable to read and write, somebody in the household will need to be identified to record for them.

Field staff will train two participants per day, one in the morning and the second in the afternoon. This will be done on Mondays while Tuesday, Thursday and Saturday (or Sunday for Seventh Day Adventists) will be the 3 days during which the participants will be recording their food intake. On the second day (Wednesdays) the field staff will visit the participant's home to conduct a 24-h dietary recall. This will be done to assess the correct observance of the diet records, after keeping the record for one week day. The results of which will be immediately compared with those recorded for one day and will be the basis for reinforcing what will be discussed during the training. All forms and the food scales will be collected on Sundays, or Mondays for Seventh Day Adventists. Five supervisors will pay random visits to participant's homes to check on the accuracy and completeness of recording.

